### Mediator

#### Changes in network brain connectivity

A score indicating differences in brain network connectivity measures between T1 and T0 will be defined and used as the mediating variable in all analyses. Children will be scanned on a 3T Magnetom Prisma (Siemens Healthineers) MRI system. Structural scans, T1-weighted, fluid attenuation inversion recovery (FLAIR) and susceptibility-weighted imaging (SWI) will be acquired for clinical neuroradiology report. During scans, participants will watch animated videos, in order to achieve better compliance in the scanner.

*Structural connectivity*. Will be measured using a diffusion weighted imaging scan. Spin-echo diffusion-weighted, echo-planar imaging sequence will be performed with 76 axial slices, voxel size 2x2x2mm, FOV = 240x240, matrix = 120x120, TR = 4500ms, TE = 51ms, MB = 2; b-value = 1,000 s/mm^2^, 64 gradient directions, 3-b0 images. Regularization, brain extraction, and motion correction will be conducted. Diffusion tensors will be calculated using a nonlinear regression procedure [53]. Whole brain tractography will be performed based on deterministic streamline fiber tractography approach [54].

*Brain network architecture of structural connectivity*. Using Brain connectivity toolbox, structural connectivity matrices will be calculated, by which, nodes indicating anatomical elements (brain regions) and edges, representing the relationships between nodes (white matter tracts), will be defined. These connectivity matrices will be further used for graph theory analyses, allowing to quantitatively characterize the global organization via network measures [55]: (1) **centrality**: strength (number of fibers connected to each node) and betweenness centrality (number of shortest paths passing through the target node); (2) **integration**: global efficiency (the shorter the path between two regions, the more efficient the connection), and (3) **segregation**: local efficiency and cluster coefficient: (reflects the tendency of nodes to cluster together). Lesions will be classified using a scheme of Adams et al. (1989) [56], to identify 3 diffuse axonal injury grades. We will further assess the relationships between network measures and the lesion grading score [57].

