### Aims and hypotheses

Based on the literature review, the present study proposes the following aims and hypotheses (as depicted in Fig 1):

**Aim 1**: Examine the moderating effect of puberty (pre- and post-pubescence) on the association between pTBI, brain network connectivity measures and neuropsychiatric outcome among females:

1.1. Examine the direct association between pTBI and neuropsychiatric outcome (Fig 1: direct effect c’ pathway). We hypothesize that females following pTBI will present poorer neuropsychiatric outcome as compared to healthy female controls.

1.2. Examine the relationship between pTBI and brain network connectivity measures (Fig 1: slope a pathway). We hypothesize that females with pTBI will present higher network connectivity measures and lower network efficiency compared to healthy female controls.

1.3. Examine the relationship between brain network connectivity measures and neuropsychiatric outcome (Fig 1: slope b pathway). We hypothesize that higher network connectivity measures and lower network efficiency will be associated with poorer neuropsychiatric outcome.

1.4. Examine the moderating effect of puberty on the mediated association between pTBI, brain network connectivity and neuropsychiatric outcome (Fig 1: mediation a*b pathway through moderator). We hypothesize that puberty will moderate the associations between brain network connectivity measures and network efficiency, and neuropsychiatric outcome in females post pTBI. That is, post-pubescence females compared to pre-pubescence females will show higher network connectivity measures, lower network efficiency and poorer neuropsychiatric outcome.

**Aim 2:** Examine the effect of changes in puberty stage and hormonal levels on brain network connectivity measures and neuropsychiatric outcome in pTBI females. We hypothesize that among females following pTBI, earlier changes in puberty stages (i.e. changes from one Tanner stage to another) and a significant increase in hormonal levels across recovery, will be related to higher network connectivity measures and lower network efficiency as well as to poorer neuropsychiatric outcome.

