### Research design

The proposed study will use a longitudinal prospective design and follow females after pTBI and age matched healthy female controls, aged 9 to 16 years [47]. Participants will be followed from admission to 18 months post injury. Participants will undergo an MRI protocol, a short neuropsychiatric assessment and a clinical assessment of puberty stage and hormonal level, across two time points: **Acute (T0)**: within one month post injury; **Chronic (T1)**: 18 months from T0 (sufficient time for neuropsychiatric changes post pTBI [48]). For a description of the schedule of study’s enrolment and assessment periods see S1 Table.

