#### Descriptive statistics

Descriptive statistics of variables will be obtained to understand the characteristics of the study population, to evaluate the distribution of participants across subgroups (e.g., puberty stage), and to identify potential confounders to inform subsequent analyses.

**Aim 1**- **moderated-mediation model:** To test our main study’s hypothesis we will apply a moderated- mediation model. Briefly, we will examine whether the magnitude of a mediation effect impact of mediator (*changes in brain network connectivity*) on the association between predictor (*pTBI*) and outcome (*neuropsychiatric outcomes*) is conditional on the value of a moderator (*puberty stage at T0*). The analysis of the moderated-mediation model will use Hayes’s (2013) PROCESS macro (Model 59) [73]. Bootstrapping method will test significance of the effects to obtain robust standard errors for parameter estimation [73]. This will produce 95% bias-corrected confidence intervals of these effects from 1000 resamples of the data. Confidence intervals that do not contain zero indicate significant effects at *p* < .05.

**Aim 2- effect of changes in puberty stage and hormonal levels on mediator and outcome:** Two step-wise linear regression models controlling for age and pre/post-injury factors in the 1st step; for the injury severity in the 2nd step; and for puberty stage and hormonal levels at T0 and T1, as well as the difference between both measures (i.e., *Δpuberty stages and Δhormonal levels*) in the 3^rd^ step, to predict (1) brain network connectivity and (2) neuropsychiatric outcomes, at T1 will be conducted.

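### Hypotheses 1.2 to 1.4 are worded as connectivity levels, but the Aim 1 mediator is the T1 minus T0 change between two post-injury scans, so the planned model does not test them as written.

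*Protocol article*

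**What the plan says.** Under Mediator, Changes in network brain connectivity, the protocol article states: "A score indicating differences in brain network connectivity measures between T1 and T0 will be defined and used as the mediating variable in all analyses". The Aim 1 paragraph of the analytical approach uses the same quantity, describing a "mediation effect impact of mediator (*changes in brain network connectivity*) on the association between predictor (*pTBI*) and outcome". In Research design, the first scan (T0) is placed "within one month post injury" and the second (T1) 18 months later. There is no pre-injury scan.

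The section Aims and hypotheses is written differently:

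- Hypothesis 1.2 (path a): "We hypothesize that females with pTBI will present higher network connectivity measures and lower network efficiency compared to healthy female controls".
- Hypothesis 1.3 (path b): "We hypothesize that higher network connectivity measures and lower network efficiency will be associated with poorer neuropsychiatric outcome".
- Hypothesis 1.4 (moderation): "post-pubescence females compared to pre-pubescence females will show higher network connectivity measures, lower network efficiency and poorer neuropsychiatric outcome".

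None of the three mentions change between scans. The abstract and the caption of Fig 1 also name connectivity, not its change, as the mediator. The article describes no Aim 1 analysis in which a T0 or T1 level is the mediator.

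**The concern.** A level and a post-injury change are different quantities. Damage that is present at the first scan and still present at the second is what hypothesis 1.2 describes, yet it leaves no trace in a difference between those two scans. An injury effect that partly recovers does leave a trace, but with its direction reversed.

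The interpretation of the main model is at stake. A null path a could be reported as no injury effect on connectivity when the effect is lasting. A significant path a could be read as support for, or evidence against, a level hypothesis when it speaks only to the course of recovery.

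**Working it through.** The plan gives no figure for path a, so there is none to reproduce. The check is algebra from the stated definitions, followed by an illustration with assumed inputs.

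**Algebra.** Let d0 and d1 be the mean differences (pTBI minus control) in a connectivity measure at T0 and T1. Path a on the change score is

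(mean of T1 − T0 in pTBI) − (mean of T1 − T0 in controls) = d1 − d0.

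Write d1 = g·d0, where g is the share of the T0 difference that remains at T1. Path a on change is then (g − 1)·d0, and on the T1 level it is g·d0. At g = 1 the first is zero whatever the size of d0. For g between 0 and 1 it has the opposite sign to d0. For g above 1 it has the same sign.

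**Inputs for the illustration.**

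- From Sample size and power: α = 0.05 (two-sided assumed) and a minimum of 100 participants, taken as 50 per group.
- Assumed, not in the article: d0 = 0.5 SD, unit SD at each scan, and between-scan correlation rho of 0.5, 0.7 or 0.9.

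**Formulas.** The SD of change is √(2(1 − rho)), which is 1.000, 0.775 and 0.447. The standard error is SE = SD·√(2/50), which is 0.2 for a level and 0.155 for change at rho = 0.7. With δ the contrast, power = Φ(|δ|/SE − 1.96) + Φ(−|δ|/SE − 1.96).

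| g | Path a on change (SD) | Power on change, rho 0.5 / 0.7 / 0.9 | Path a on T1 level (SD) | Power on T1 level |
|---|---|---|---|---|
| 1 (fully lasting) | 0 | 5% / 5% / 5% | 0.5 | 71% |
| 0.75 | −0.125 | 10% / 13% / 29% | 0.375 | 47% |
| 0.5 (half lasting) | −0.25 | 24% / 37% / 80% | 0.25 | 24% |
| 0 (fully resolved) | −0.5 | 71% / 90% / nearly 100% | 0 | 5% |
| 1.5 (worsening) | +0.25 | 24% / 37% / 80% | 0.75 | 96% |

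Example, half lasting at rho = 0.7: 0.25/0.155 = 1.61, and Φ(1.61 − 1.96) is about 0.37.

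Change has the more powerful path a when (1 − g)/√(2(1 − rho)) exceeds g, that is, when g is below 1/(1 + √(2(1 − rho))). This is 0.50, 0.56 and 0.69 for the three correlations. Change therefore wins once more than about 50%, 44% or 31% of the T0 difference has resolved.

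**Indirect effect.** A simulation of 4,000 trials took the fully lasting case (0.5 SD at both scans), N = 100, and an outcome depending on the T1 level with slope 0.5, so the true indirect effect is 0.5 × 0.5 = 0.25. Across rho 0.5 to 0.9:

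- Change mediator: mean indirect effect about 0.00; paths a and b jointly significant in 0.8% to 2.8% of trials.
- T1 level: mean about 0.25; jointly significant in 68% to 70%.
- T0 level: mean 0.12 to 0.23; jointly significant in 42% to 68%.

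The simulation has no puberty moderator, so it is not an evaluation of the planned moderated model.

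**The article's own Table 1.** T1 levels and T1 − T0 changes for the pilot girls are:

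| Measure | T1, post-menarche | T1, pre-menarche | Change, post-menarche | Change, pre-menarche |
|---|---|---|---|---|
| Strength | 22.61 | 18.78 | 22.61 − 23.91 = −1.30 | 18.78 − 19.52 = −0.74 |
| Efficiency | 93.04 | 83.36 | 93.04 − 111.20 = −18.16 | 83.36 − 84.86 = −1.50 |

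As T1 levels, both measures are higher post-menarche: with hypothesis 1.4 for strength, against it for efficiency. As changes, both are more negative post-menarche: against it for strength, with it for efficiency. Moving from level to change reverses the reading of each. With 2 and 3 girls of very different injury severity, this only illustrates that the choice matters.

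**The case against.** The best defence is that change was chosen deliberately. The mediator heading, the Aim 1 paragraph and the exploratory analyses all speak of connectivity changes, and the background is about re-organisation after injury. A change mediator is legitimate for that question. It also removes stable differences between girls that predate the injury, which matters in a non-randomised comparison. All of this stands, and it places the defect in the mismatch between hypotheses and mediator, not in change scores as such.

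Three further points stand. Complete cancellation needs an identical difference at both scans. The article does not say how persistent the effect is, and the pilot decline from acute to chronic phase cannot settle it, because the one healthy girl has no second scan. Cancellation also strikes path a, whereas Sample size and power names moderation of the connectivity–outcome association as the primary hypothesis. Path b on change is weakened, not removed: if the outcome depends on the T1 level alone and both scans have equal variance, its slope is (1 − rho)/(2(1 − rho)) = one half of the level slope.

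A reader might go further in ways the article does not support:

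- That a single score would cancel itself, because connectivity is expected to rise and efficiency to fall. The article says a score will be defined, not that it is a raw sum, and signs can be aligned.
- That five measures tested separately inflate the error rate. No such set of five tests is stated, and multiplicity handling is commonly left to the analysis plan.
- That Aim 2, which aims "to predict (1) brain network connectivity and (2) neuropsychiatric outcomes, at T1 will be conducted", contradicts the use of change in all analyses. That clause governs the mediating variable. In the Aim 2 regression connectivity is the dependent variable, so the wording is loose but not clearly contradictory.

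**Conclusion.** The point holds as a mismatch between the stated hypotheses and the stated mediator. The result that path a on change equals d1 − d0 follows from the protocol's definitions and needs no assumed effect size. The consequences are that an unchanged injury difference does not register and a partly resolving one reverses sign.

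The size depends on persistence, which is unknown. For 0.5 SD at T0, N = 100 and rho = 0.7, path-a power on change versus T1 level runs from 5% versus 71% (fully lasting), through 37% versus 24% (half lasting), to 90% versus 5% (fully resolved). It would be wrong to infer that the change mediator is invalid, that it must give a null result, or that a T1 level is always the stronger choice. What can be said is that hypotheses 1.2 to 1.4 concern levels, and no Aim 1 analysis described in the article uses one.

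**What to change.** Choose one of two routes before analysis.

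1. Keep the change mediator. Reword hypotheses 1.2 to 1.4 as differences in T0 to T1 change (between injury groups for 1.2, in relation to outcome for 1.3, by puberty group for 1.4), with the expected direction of change given. Limit the conclusions to recovery or re-organisation.
2. Keep the hypotheses. Test them with a prespecified connectivity-level mediator, at T0 or T1, and retain the change score for a separately worded recovery hypothesis. The T0 level precedes the T1 outcome, while the T1 level is measured alongside it; the choice should be stated with its reason.

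Adding T0 as a covariate to a T1 mediator is not a substitute. It leaves only d(1 − rho) of a lasting difference, for example 0.5 × (1 − 0.7) = 0.15 SD.

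The first route costs wording only. The second costs one extra model run on scans already planned. Its drawback is that a level does not remove stable pre-injury differences between girls; the retained change analysis does.

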#### 2. Moderator

*Pubertal stage*. Pubertal stage will be assessed at injury/first visit for controls (T0), and at 18 months from T0 (T1). Pubertal stage will be defined based on 3 different measures, known to be highly correlated [58]: (1) the Pubertal Development Scale (PDS) [59]. This self-report questionnaire contains questions concerning secondary sexual characteristics, including items concerning hair growth, skin changes, and growth spurt, with sex-specific items (i.e. menarche and breast development in females). The PDS measures a composite puberty score including effects of adrenal, and gonadal hormones, as well as growth hormone. Participants will be instructed to indicate pubertal stage on each of these physical characteristics on a 4-point scale: ranging from (a) has not started to develop, (b) shows first signs of development, (c) shows clear development to (d) has finished developing; (2) *Hormonal Levels* (LH, FSH and Estradiol) will be drawn from blood samples at T0 and T1. For females who are post menarche, and T1 assessment meetings will be scheduled at 3–5 days of the menstrual cycle; and (3) *Tanner Stage* assessment according to a physical examination conducted by a qualified clinician. Tanner staging categorizes individuals along an ordinal puberty scale from 1 to 5, on the basis of pubic hair and breast development in females [60]. The majority of girls reach Tanner Stage II at age 10.5 (a proxy for pubertal onset), and then progress through an average rate of 0.96 stages per year [61]. A binary puberty (pre and post-pubescence) score at T0 will be computed out of the pubertal stage measures and used as the moderator variable in the statistical model. If the different measures will conflict (i.e., yield different puberty stage classifications), the final score will be based on the Tanner stage score, which will be further used in analyses [47].

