Sex hormones, (specifically gonadal hormones such as estrogen and progesterone) have been suggested as significant factors mediating neurological and neuropsychiatric outcomes after TBI in females [12, 13]. A possible explanation, known as the *hormonal withdrawal hypothesis* (i.,e, frequent miss of menstrual periods or total absence of menstruation), has been reported in females following TBI [13], and suggested to be a key factor contributing to worse outcomes in females. Furthermore, as males have low pre-injury levels of gonadal hormones, they may be less affected by hormonal suppression post injury. The phase of the menstrual cycle at injury, was found to be significantly related to psychological and neurologic outcomes among females following mild TBI [13]. Females with the highest progesterone levels at the time of injury (i.e., luteal phase of the menstrual cycle) had the worst outcomes as compared to females in the follicular phase (i.e., relatively low progesterone levels) and compared to females taking synthetic progestin (i.e., maintaining high levels of progestin before and after injury). Thus, if the hormonal withdrawal hypothesis is linked to poorest outcomes, a relatively simple intervention could lead to significant improvement in outcomes [13] necessitating the need to address hormonal levels and time of menstrual cycle across studies with female TBI patients of all ages.

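### The cycle-day rule for hormone sampling is garbled and, as printed, names only T1, so the hormone change used in Aim 2 may mix menstrual-cycle phase with recovery

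*Protocol article*

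**What the plan says.** All references are to the protocol article.

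- **What is drawn and when.** The Moderator section lists "LH, FSH and Estradiol) will be drawn from blood samples at T0 and T1".
- **The cycle-day rule.** The next sentence there reads "For females who are post menarche, and T1 assessment meetings will be scheduled at 3–5 days of the menstrual cycle". It names T1 alone, and the word before T1 joins it to nothing.
- **When T0 is.** The same section opens with "Pubertal stage will be assessed at injury/first visit for controls (T0), and at 18 months from T0 (T1". Research design describes the acute visit as "within one month post injury". Neither mentions cycle day.
- **How the hormones are used.** The Aim 2 hypothesis is that "a significant increase in hormonal levels across recovery, will be related to higher network connectivity measures and lower network efficiency". The Aim 2 regressions (under Descriptive statistics) enter, in their third step, terms "for puberty stage and hormonal levels at T0 and T1, as well as the difference between both measures". Secondary analyses also takes hormone levels as a puberty measure in their own right.
- **What the background argues.** The Introduction says earlier findings on cycle phase are "necessitating the need to address hormonal levels and time of menstrual cycle across studies with female TBI patients of all ages". It also reports, in females after TBI, "frequent miss of menstrual periods or total absence of menstruation".
- **Covariates.** Neither the Covariates section nor the confounders listed under Secondary analyses includes cycle day or cycle phase.

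**The concern.** A days 3–5 rule makes sense only if cycle timing is thought to affect the hormones being measured. If the rule holds at one visit and not the other, the difference between visits contains a part that reflects where in her cycle a girl happened to be at T0. The article gives no term that would remove it.

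That part arises only in girls who are post-menarche at T0, so the quality of the hormone predictor would depend on pubertal status, which is the study's central variable. At stake are the Aim 2 hormone-change result and the secondary hormone analyses.

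There is a second, smaller difficulty. The rule is written for assessment meetings, not for blood draws. Research design places MRI and neuropsychiatric assessment at the same visits. A girl whose periods are absent or irregular may have no usable day 3–5, so the rule as worded gives no date for any part of her T1 visit.

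**Working it through.** There is no stated figure to reproduce. The check is mainly a comparison of the text under two readings, with a small illustration of size.

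**Reading A: the rule covers T1 only, as printed.** Split the girls by status at T0.

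- Pre-menarche at T0: no cycle phase at T0, so no T0 phase error enters the change.
- Post-menarche at T0: the observed T0 level is the underlying level plus a shift for cycle day. At T1 the cycle day is held to 3–5. The observed change (T1 minus T0) is then the real change minus the T0 shift, relative to days 3–5.

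Because the Aim 2 model contains the T0 level and the change, the T0 shift enters both terms.

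**Reading B: a T0 was lost before the stray conjunction.** Both draws fall on days 3–5 and the T0 shift largely disappears in girls cycling at both visits. The rule must then be reconciled with a T0 described as at injury or first visit. The one-month T0 window in Research design could accommodate it for many girls: a 28-day cycle fits inside a month, while a 35- or 45-day cycle may not.

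**How often would an unscheduled T0 draw land in the window?** This applies to Reading A only. Assumptions: T0 cycle day is uniform, and cycle length is L days (not given in the document). Chance = 3/L.

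| L (days, assumed) | 3/L | Outside days 3–5 |
|---|---|---|
| 21 | 14.3% | 85.7% |
| 28 | 10.7% | 89.3% |
| 35 | 8.6% | 91.4% |
| 45 | 6.7% | 93.3% |

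The last column is the share of draws off three particular days. It is not the share in a different phase, since days next to the window are hormonally similar to it.

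**What could that do to the predictor?** Let k be the variance of the T0 shift divided by the variance of the real hormone change among girls post-menarche at T0. If the shift is unrelated to the real change, the reliability of the observed change is 1/(1 + k):

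- k = 0.25: 1/1.25 = 0.80
- k = 0.5: 1/1.5 = 0.67
- k = 1: 1/2 = 0.50

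The documents give no value for k, so these show the form of the loss and are not an estimate. With correlated predictors in the same model, the bias in any one coefficient need not be toward zero.

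**Reach into Aim 1.** The primary moderator is a binary pre/post score at T0, and Tanner stage decides when the puberty measures conflict. An off-phase hormone value therefore has little route into the primary model.

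**The case against.** The strongest counter-argument is that the rule was never meant for T1 alone. The stray conjunction and the plural noun suit a lost T0, and the preceding sentence speaks of both visits. On that view the draws are matched and the main harm vanishes. The phrase about injury or first visit may also just label the timepoint, since Research design allows a month. This stands as a real possibility, so it would be wrong to assert that the plan deliberately controls only T1. It does not settle the matter: a site cannot tell from this text when to draw T0 blood, and no cycle variable is available to repair an off-window draw.

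Some stronger inferences are tempting and are not supported:

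- *That about 89% of hormone changes compare different phases.* That figure (28-day cycle) counts draws off days 3–5, assumes unscheduled draws, and applies only to girls post-menarche at T0, whose number is not given.
- *That luteal-phase injury produces a fall in the measured hormones, or that early-follicular injury hides any change.* The Introduction's phase contrast concerns progesterone, which is not drawn. Two phase-matched samples would still show a real change.
- *That the study rests on hormonal withdrawal and would lose the girls who carry it.* The Introduction suggests that young females may show the opposite profile, and Aim 2 hypothesises an increase. Nothing says a girl without a cycle day is deferred or dropped, and a fallback may sit in the full protocol, which is not shown.

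**Conclusion.** The point holds in limited form. The cycle-day sentence is defective and must be reconciled with the T0 timing given in the Moderator section and in Research design.

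Followed as printed, it yields a hormone change that mixes cycle phase with recovery in girls post-menarche at T0, contrary to the article's own call to address cycle timing. The consequence falls on Aim 2 and the secondary hormone analyses. A reader might infer that the primary moderated-mediation result is undermined; the Tanner tie-break means it is little affected.

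The size cannot be fixed from the document. Under Reading A, with uniform T0 timing and assumed cycles of 21 to 45 days, about 7–14% of T0 draws in post-menarche girls would fall in the T1 window. Under Reading B that figure does not apply, and what remains is a wording conflict plus the unaddressed case of girls without a usable cycle. Clarification is worthwhile under either reading, and early, because a T0 sample cannot be retaken later.

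**What to change.** 1. **Reconcile the text.** Amend the Moderator section and Research design so that they agree on T0 timing, and state that the same cycle-day window applies to the hormone draw at T0 and T1, in both groups, where feasible within the T0 month.
2. **Record the date.** Collect the first day of the last period at every draw.
3. **Adjust, do not exclude.** In Aim 2, adjust the hormone terms for cycle day or, more simply, for on- or off-window status with amenorrhoea as its own category. Pre-menarche girls have no cycle day and can stay in the reference category, since puberty stage is already in the model. Keep off-window girls in the main analysis and show on-window girls alone as a sensitivity analysis. Dropping off-window girls would remove only post-menarche participants, from about 60 × 0.80 = 48 pTBI girls left after the planned attrition.
4. **Limit the rule's reach.** State that it governs the blood draw and does not defer the T1 MRI or neuropsychiatric assessment of girls with irregular or absent periods.

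**Cost.** One case report form field, some T0 draws on a separate day from the scan with slightly more variable time since injury, and one or two extra model terms. A simple on/off term removes only the average shift; cycle day removes more but is undefined for girls without a cycle.
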